Even though the effectiveness of MET has been established in well-designed clinical trials, their results cannot be directly extrapolated to PC. Mainly, the larger clinical trials on MET effectiveness (i.e., project MATCH [13] and the United Kingdom Alcohol Treatment Trial [UKATT] [14]) compare it with other active treatments, where specialized counselors provide MET and the active comparator. On these trials, MET showed an effectiveness similar to the other more extensive treatments. However, we do not know if this effectiveness will remain when applied by a general psychologist. In fact, the provider’s professional credentials modify the effect of motivational treatments, with a higher qualification associated with better outcomes [16]. On the other hand, clients with AUDs have access to a variety of unspecialized services in PC; it could be the case in this setting that usual care is adequate for a large number of clients with a mild form of dependence. For instance, a client could have a consultation with a psychologist, access several social services through a social worker, have an appointment with a physician and get a prescription for psychoactive drugs and disulfiram, or be referred to secondary care. In other words, as MET has not been compared with usual care in PC, and as some clients recover from AUDs spontaneously in the community, we cannot anticipate the net effect of MET in this setting. Altogether, the therapy cannot be introduced to Chilean PC without adaptation and local evidence that confirms the effect.

This trial aims to study the effectiveness of a Brief Motivational Treatment (BMT), which is an adaptation of MET’s procedures to Chilean PC, compared to enhanced usual care (EUC).

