### Intervention description {11a}

#### BMT

Participants in the intervention group will receive the BMT, which is a PC adaptation of the MET as manualized in the Project MATCH [19]. This treatment consists of four 45-min sessions, provided by a psychologist at weeks 1, 2, 6, and 12. The first three sessions, occurring during the first 6 weeks, are more active regarding the behavioral change, while the last session functions as closure and review of the process. If a participant asks for more support, they will be able to attend up to two extra sessions before the last one.

The main adaptations to the original Project MET manual are:
The translation into Chilean Spanish.An update of MI concepts used throughout the manual using the last edition of the MI reference book.The addition of companion training material that includes a demonstrative video and practical exercises on the MI strategies.A personalized feedback procedure based on the evaluation used in the trial and the local epidemiological situation.The addition of information on additional resources available in the PC center and the community to be included in the “menu of options.”The addition of a module regarding the coordination of health services in the Chilean PC context. This supplementary material is meant to facilitate the participants’ access to services complementary to BMT within the PC center (i.e., social services, medical services, among others).

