#### Selection and supervision of the providers

We will recruit general psychologists or other psychosocial professionals with at least 3 years of experience in PC. They will receive training in BMT and then will demonstrate proficiency in a simulated client session (or will provide a taped interview showing a proficient application of BMT).

During recruitment, therapy sessions will be recorded, and 10% of them will be reviewed using an MI proficiency scale. Then, a feedback report on the fidelity to MI will be issued and discussed with each therapist. The instrument to be used will be chosen during the pilot among the available validated tools [20].

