### Outcomes {12}

#### Primary outcome

The primary outcome is the change from baseline in the drinks per drinking day (DDD) during the last 90 days (i.e., the previous 12 weeks), measured at 6 months follow-up. The DDD will be aggregated using means.

The DDD constitutes a relevant outcome because the frequency and quantity in which alcohol is consumed mediate the occurrence of behavioral disorders and health deterioration in clients with AUD. Even though a more comprehensive result, such as clinical recovery or improved quality of life, would be of more clinical significance, these outcomes exceed a short-term, exploratory trial. We have chosen DDD because it has shown to be sensitive to treatment and because it allows comparability with influential clinical trials [21].

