## Statistical methods

### Statistical methods for primary and secondary outcomes {20a}

We will compare the BMT group with the EUC group for every main outcome listed in Table 1. *T* tests will compare continuous results, and chi-squared tests will compare dichotomous outcomes. We will compute mean differences (MD) for continuous outcomes, and relative risks (RR) and RR reductions (RRR) for dichotomous results, with their corresponding 95% confidence interval. *P* values will be reported to four decimal places, with *P* values less than 0.001 reported as < 0.001. The latest version of R [31] will be used to perform the statistics. Table 1 summarizes the methods for the analysis of each outcome.

**Table 1 Tab1:** Statistical methods for outcomes and ancillary analyses

Outcome	Hypothesis	Outcome measure	Methods of analysis

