### Adverse event reporting and harms {22}

The brief motivational therapy is not supposed to increase health risks in clients; however, due to the behavioral nature of the alcohol use disorder, it is expected that some common problems could arise in the participants. High-risk events, such as suicidal ideation or behavior, violence and aggression to others, increase in depressive symptoms or anxiety, severe intoxication, or withdrawal symptoms, will all be managed with a crisis intervention delivered in the health center in accordance with local protocols. Close coordination between the study therapists and the rest of the health team will be encouraged through all protocol execution so that crisis protocols can be activated when necessary.

The study therapists will be responsible for assessing the participant when an adverse event is suspected and, if confirmed, will contact the trial coordinator and the local organization to mobilize the required resources (e.g., medical assessment, referral to the emergency room, and contact to a family member). The participants will have access to a centralized phone number where they can contact their therapist for help in case of emergency issues regarding treatment.

The trial coordinator will complete a report with the details of the event, including the diagnosis, management, and harms to the participant.

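### The fixed t and chi-squared tests ignore clustering of BMT participants within therapists, and no listed sensitivity analysis checks whether this matters

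*Protocol article*

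**What the plan says.** Under Statistical methods {20a}, t "tests will compare continuous results, and chi-squared tests will compare dichotomous outcomes", with mean differences or relative risks and 95% confidence intervals. Table 1 repeats this outcome by outcome. Its sensitivity analyses are a per-protocol comparison, a linear model adjusting for baseline variables, and multiple imputation.

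The primary outcome is defined in section {12}: "The primary outcome is the change from baseline in the drinks per drinking day (DDD) during the last 90 days".

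On delivery, section {11a} states: "This treatment consists of four 45-min sessions, provided by a psychologist at weeks 1, 2, 6, and 12". The providers are plural: "We will recruit general psychologists or other psychosocial professionals with at least 3 years of experience in PC", and "a feedback report on the fidelity to MI will be issued and discussed with each therapist". The harms section {22} treats each participant as having one therapist, since "they can contact their therapist for help in case of emergency issues regarding treatment".

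The Background says that "the provider’s professional credentials modify the effect of motivational treatments, with a higher qualification associated with better outcomes". Objectives {7} and the Discussion name fidelity to motivational interviewing and the working alliance as mediators or modifiers of the effect. The Discussion also leaves open whether a general psychologist in primary care can deliver the therapy proficiently.

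The sample size section {14} contains no ICC and no design effect. Randomization {16a} is stratified by site and baseline SDSS-DAYS severity.

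**The concern.** BMT is added to enhanced usual care (section {11b}), and section {11d} rules out other psychosocial interventions for alcohol use disorder in the health center. Clustering by study therapist therefore arises in the BMT arm and, as far as the text shows, not in the EUC arm. That is a partially nested design.

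The ordinary t test treats all BMT participants as independent, which amounts to assuming a therapist ICC of exactly zero. This sits badly with a protocol that expects fidelity and alliance, both of which can differ between therapists, to shape the result.

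The trial is meant to inform a decision on whether Chilean primary care should adopt BMT, delivered by psychologists like those usually found there. That is a statement about therapists beyond those in the trial, so variation between therapists belongs in the standard error. If it is left out, the interval may claim more precision than the data hold, and nothing planned would show it.

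**Working it through.** **Inputs from the protocol.** α = 0.05, SD 6.29, difference 2.99 drinks (9.89 − 6.90), 91 recruited per arm, 20% loss to follow-up. Analysed per arm: 91 × 0.8 = 72.8, taken as 73.

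**The plan's own figure.** The stated 76 per group does not follow from these inputs. With n = 2(z_α + z_β)²σ²/δ², I get 70 (two-sided) or 55 (one-sided). That is a separate matter. The ratios below depend on n only through the caseload, and using 76 instead of 73 hardly changes them.

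**Inputs assumed.** Number of therapists k, equal caseloads m = 73/k, and therapist ICC ρ in the BMT arm only. None of these is in the document.

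**Formulas.**
- Design effect in the BMT arm: 1 + (m − 1)ρ.
- True SE divided by t-test SE: r = √[(2 + (m − 1)ρ)/2].
- Shortfall of the t-test SE: 1 − 1/r.
- Actual two-sided error of the nominal 5% test: 2[1 − Φ(1.96/r)].

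Example with k = 4, ρ = 0.05: m = 18.25; r = √[(2 + 17.25 × 0.05)/2] = √1.431 = 1.196; error = 2[1 − Φ(1.638)] = 10.1%.

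| k | r at ρ = 0.05 | t-test SE too small by | error at ρ = 0.05 | error at ρ = 0.02 | error at ρ = 0.01 |
|---|---|---|---|---|---|
| 3 | 1.26 | 21% | 11.9% | 7.8% | 6.4% |
| 4 | 1.20 | 16% | 10.1% | 7.0% | 6.0% |
| 6 | 1.13 | 12% | 8.3% | 6.3% | 5.7% |
| 8 | 1.10 | 9% | 7.4% | 5.9% | 5.5% |
| 15 | 1.05 | 5% | 6.1% | 5.5% | 5.2% |

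At ρ = 0 the error is 5% for any k. Simulation of the t test at 76 per arm (40,000 replicates) agrees: 10.1% for k = 4 and 7.6% for k = 8 at ρ = 0.05.

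**Power.** With independent participants the t-test SE is 6.29 × √(2/73) = 1.041, and power for 2.99 drinks is Φ(2.99/1.041 − 1.96) = 82%. Multiplying the SE by r at ρ = 0.05 gives 63% (k = 3), 67% (4), 72% (6) and 74% (8). These use a normal critical value, so they are upper figures.

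**Offset from stratification.** Ignoring prognostic strata makes a t test conservative. If site and severity explained a share R² of outcome variance, then r = √[(2(1 − R²) + (m − 1)ρ)/2]. With R² = 0.10 (an assumption):
- ρ = 0.02: 5.8% (k = 4), 5.1% (6), 4.8% (8).
- ρ = 0.05: 8.9% (k = 4), 7.1% (6), 6.2% (8).

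**Cost of the nested analysis.** Let v_B = 1 + (m − 1)ρ and v_C = 1 be the relative variances of the two arm means. Satterthwaite degrees of freedom are (v_B + v_C)²/[v_B²/(k − 1) + v_C²/72]. At ρ = 0.05:
- k = 3: 3.167²/(2.167²/2 + 1/72) = 4.2 df, critical t 2.71. The interval is 1.258 × 2.71/1.98 ≈ 1.7 times as wide as the t-test interval, and power is about 43%.
- k = 4: 7.0 df, critical t 2.36. The interval is about 1.4 times as wide, and power is about 54%.

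**The case against.** Four points on the other side have weight.

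- **The size is unknown.** No ICC or number of therapists is given. A manual, an experience requirement, training, a proficiency check and feedback on 10% of sessions all work to reduce differences between therapists. The Background remark on credentials concerns levels of qualification, not variation among people who meet one entry profile. This stands. It is tempting to read the plan as certain to give too narrow an interval and an error above 5%, but the document does not support that. Both depend on an ICC above zero, and the stratification offset can cancel the excess at an ICC of 0.02 with 6 to 8 therapists.
- **Which null is tested.** If BMT changed nobody's outcome, there would be no treatment-induced therapist variance and the t test would not be inflated by it. The inflation concerns an average effect of zero across a population of therapists who differ. This stands as a limit on the claim. It does not remove the point, because the trial's stated purpose is inference beyond its own therapists.
- **A nested primary model could cost much of the power.** With 3 or 4 therapists it leaves about 4 to 7 degrees of freedom. This stands, and it is why a sensitivity analysis is proposed.
- **A fuller plan may cover it.** Further documents are referred to, and their silence cannot be assumed. But the article fixes the primary test and lists the sensitivity analyses by name, so the criticism is of a stated method and not of a missing detail.

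**Conclusion.** The point holds in conditional form. The stated tests ignore therapist clustering in the BMT arm, and none of the named sensitivity analyses addresses it. If the therapist ICC is above zero, the interval for an effect generalised to other primary-care psychologists is likely too narrow, and the type I error can exceed 5%.

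The size rests on assumptions: 73 analysed per arm, equal caseloads, clustering in one arm only. At an ICC of 0.05 with 8 down to 3 therapists, the two-sided error is about 7 to 12%. At an ICC of 0.01 to 0.02 with 8 or more therapists, the excess is at most about one percentage point before any offset from the strata. The offset is itself unquantified, so it is not a safeguard. At an ICC of 0.05 it only reduces the excess for 3 to 8 therapists under the 10% assumption.

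This is worth correcting but does not invalidate the trial.

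**What to change.** - Record the therapist identifier for each BMT participant.
- Add to section 4 of Table 1 a named sensitivity analysis of the primary outcome: a partially nested linear mixed model with a random therapist effect in the BMT arm only, site and SDSS-DAYS severity stratum as fixed effects, and small-sample degrees of freedom.
- Report the number of therapists and the estimated ICC, and qualify the primary conclusion if this analysis and the t test differ.

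The cost is one variable and a few lines of analysis text, filed as an amendment, since section {25} counts changes to the statistical analysis as such. The interval will be wider, and markedly so with only 3 or 4 therapists, where the ICC will also be poorly estimated. For that reason the model is proposed as a sensitivity analysis and not as the mandatory primary analysis. The document does not say how therapists are spread over sites. If each site has one therapist, the random effect will also absorb site differences in the effect of BMT, and the report should say so.

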**1) Primary**			
a) Drinks per drinking day at 6 months	BMT reduced outcome from baseline to 6 months	Drinks per drinking day during the last 90 days in the Timeline Follow Back [continuous]	*T* test
**2) Secondary**			
a) Alcohol use pattern at 6 months	Back to a low-risk use or abstinence after the treatment	Presence of a low-risk pattern: less than 100 g of ethanol a week and no binge drinking occasions (i.e., more than three SD in women and 4 in men) during the last 90 days in the Timeline Follow Back [binary]	Chi-squared test
b) Frequency of heavy drinking at 6 months	Reduction	Number of heavy drinking occasions (i.e., more than three SD in women and more than four in men) during the last 90 days in the Timeline Follow Back [continuous]	*T* test
c) Most extended period of abstinence during the last 3 months	Augmentation	Number of days of abstinence within the last 90 days in the Timeline Follow Back [continuous]	*T* test
d) Severity of dependency at 6 months	Reduction	Score in the Alcohol DAYS, SEV, and WORST SEV score in the Substance Dependence Severity Scale (last 30 days) [continuous]	*T* test
e) Alcohol related negative consequences	Reduction	Total consequences score in the Drinker Inventory of Consequences [continuous]	*T* test

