#### Secondary outcomes

The number of participants with a low-risk alcohol use pattern estimated by the number of days of consumption, of abstinence, and intoxication during the last 90 days, aggregated using the proportion of participants per group, at 6 months follow-up. Additionally, the most extended period of abstinence since enrolment will be estimated at 6 months follow-up. The number of abstinence days of each participant will be aggregated using means.The change from baseline in the negative secondary consequences of alcohol consumption will be measured using the DrInC-2R questionnaire [22] measured at 6 months follow-up and aggregated using means.The change from baseline in the severity of the AUD using the Substance Dependence Severity Scale (SDSS) at 6 months follow-up [23]. Means will be used to aggregate participants’ DAYS, SEV, and WORST SEV scores for alcohol. The severity of AUD is a critical outcome in two ways: first, we hypothesize that the severity should decrease with treatment; second, severity is expected to predict treatment effect, so it could help identify a specific range of severity in which BMT is more effective.The change from baseline in the motivational stage measured with the SOCRATES scale [22] at 6 months follow-up. The proportion of participants that improve their motivational stage will be used to aggregate the measurement in each group. This scale was designed to classify clients in one of the stages of change according to Prochaska and DiClemente [24] and is expected to mediate client recovery and predict treatment effect.

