## Assignment of interventions: allocation

### Sequence generation {16a}

Participants will be randomly assigned to either control or experimental group with 1:1 allocation as per a computer-generated randomization schedule stratified by site and the baseline SDSS-DAYS score using permuted blocks of random sizes. The cut point for the severity score will be determined during the trial pilot. To ensure concealment, we specified the block sizes in a separate document with restricted access.

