**4) Sensitivity analyses**			
a) Per-protocol analysis			a) *T* test/chi-squared
b) Adjustment for baseline variables			b) Linear model (multivariate regression)
c) Missing data imputation			c) Multiple imputation (missing-at-random assumption)

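### The protocol leaves open whether the t tests for dependence severity (SDSS) and alcohol consequences (DrInC) use change from baseline or the score itself; a baseline-adjusted model would remove the ambiguity at almost no cost.

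*Protocol article*

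**What the plan says.** In the protocol article, the secondary outcomes under Outcomes {12} are worded as changes. For consequences: "The change from baseline in the negative secondary consequences of alcohol consumption will be measured using the DrInC-2R questionnaire", at 6 months and aggregated using means. For severity: "The change from baseline in the severity of the AUD using the Substance Dependence Severity Scale (SDSS) at 6 months follow-up", with means used for the DAYS, SEV and WORST SEV scores.

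The section on statistical methods for primary and secondary outcomes {20a} assigns t tests to continuous outcomes and refers to Table 1 for a summary of the method for each outcome. In Table 1:

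- Row 2d is labelled "Severity of dependency at 6 months", and its measure is "Score in the Alcohol DAYS, SEV, and WORST SEV score in the Substance Dependence Severity Scale (last 30 days) [continuous".
- Row 2e has no time point in its label, and its measure is "Total consequences score in the Drinker Inventory of Consequences [continuous".

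Both rows give a one-word hypothesis of reduction and a t test. Neither row mentions change. Baseline enters an outcome model only as a sensitivity analysis in the same table: "Adjustment for baseline variables", by linear model.

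Randomisation is "stratified by site and the baseline SDSS-DAYS score using permuted blocks of random sizes", with the cut point to be set in the pilot. This affects the size of the problem for SDSS-DAYS.

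**The concern.** A t test on the change and a t test on the 6-month score are different analyses of the same data. They give different estimates, standard errors and p values. A programmer working from the outcome list would code the change, and one working from Table 1 could reasonably code the score. Four reported results are affected: SDSS DAYS, SEV and WORST SEV, and DrInC total. If the text does not fix the variable beforehand, the choice could be made with the results in view. The less efficient of the two tests also gives up precision that the baseline measurement could supply.

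**Working it through.** **No plan figure to reproduce.** The protocol's only sample size calculation is for drinks per drinking day. It gives no SD, target difference or correlation for SDSS or DrInC. The checks below are in SD units and take 76 per arm, the protocol's figure before loss to follow-up, only to set a scale. The ratios in steps 2 and 3 do not depend on the sample size. (The listed parameters give 70 per arm two-sided or 55 one-sided rather than 76. That is a separate matter with no bearing here.)

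**Step 1: the gap between the two estimates.** Let B be the between-arm difference in baseline means and F the difference in 6-month means, in the same participants. The change analysis estimates F − B and the score analysis estimates F. They differ by exactly B, which has expectation zero under randomisation. Neither coding is biased.

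**Step 2: size of the gap, score not stratified on (DrInC).** Assume the same SD σ at baseline and 6 months.

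- SD of B = σ√(2/n) = σ√(2/76) = 0.162σ.
- The standard error of F is also σ√(2/n), so the gap has an SD of 1.0 standard error of the 6-month comparison.
- Mean absolute gap = √(2/π) = 0.80 standard errors. The gap exceeds one standard error in about 32% of trials.

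**Step 3: size of the gap, score stratified on (SDSS-DAYS).** Assume a normal score cut at its median. Only the variation within each half contributes to B.

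- Variance of a half-normal variable = (1 − 2/π)σ² = 0.363σ², so the ratio is √0.363 = 0.60. Simulation gave 0.61.
- Mean absolute gap by simulation is 0.49 standard errors. The gap exceeds one standard error in about 10% of trials.

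SEV and WORST SEV are not stratification factors themselves. Their ratios lie between 0.6 and 1.0, depending on their correlation with DAYS.

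**Step 4: standard errors.** With equal SDs and a baseline to 6-month correlation r, relative to the standard error of the score t test:

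- change t test: √(2(1 − r));
- linear model with the baseline score as covariate: √(1 − r²).

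Since 1 − r² ≤ 1, and 1 − r² = (1 − r)(1 + r) ≤ 2(1 − r), the adjusted model is at least as precise as either t test in large samples.

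**Step 5: illustration only.** This borrows the standardised effect planned for drinks per drinking day (2.99/6.29 = 0.475), with 76 per arm, two-sided 5%, equal SDs and an assumed r. The first four result columns are without stratification on the score.

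| r | Power, score | Power, change | Power, adjusted | Score and change t tests disagree at 5% | Disagree, stratified at median |
|---|---|---|---|---|---|
| 0.3 | 83% | 70% | 87% | 25% | 18% |
| 0.5 | 83% | 83% | 92% | 20% | 13% |
| 0.6 | 83% | 91% | 96% | 18% | 12% |

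**Step 6: why adjustment removes the ambiguity.** Change equals the 6-month score minus baseline. When baseline is a covariate, replacing the score with the change lowers the baseline coefficient by exactly 1. The treatment coefficient and its standard error stay the same.

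**The case against.** The strongest reply is that the protocol, read as a whole, does mean change. Section {20a} presents Table 1 as a summary of methods, while the outcome definitions stand in section {12} and are explicit. The primary outcome's row supports this. Its label also refers to 6 months and its measure cell names only the drinking quantity, but its hypothesis cell states a reduction from baseline to 6 months. Read the same way, the reduction in rows 2d and 2e would be a reduction from baseline. Row 2b does not refute this, because its count of heavy drinking occasions could also be compared with baseline.

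That reply stands in part. A reader might infer an outright contradiction, with Table 1 prescribing a 6-month score for both scales. The text does not support that: row 2e has no time point, and row 2d is only the clearer of two ambiguous rows. But the reply depends on carrying the primary row's fuller hypothesis over to rows that do not repeat it, so the variable remains unfixed.

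Three further points against the concern are fair:

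- These are secondary outcomes in a trial that calls itself exploratory.
- The analyst is blinded to allocation, and changes to the statistical analysis require a formal amendment. Both reduce the scope for a results-driven choice, but neither says which variable is analysed.
- The full protocol and code are said to be in a repository that is not shown. If they settle the coding, the article only needs to be aligned with them.

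Finally, adding the words for change to rows 2d and 2e would be enough to reconcile the text. That is true, but it would keep the change t test, which is the less precise of the two t tests when r is below 0.5.

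**Conclusion.** The point holds as an unreconciled ambiguity in the analysed variable for SDSS and DrInC, clearer for SDSS than for DrInC. With the planned unadjusted t test, the SD of the gap between the two possible estimates is about 1 standard error of the 6-month comparison for DrInC and about 0.6 for SDSS-DAYS, with SEV and WORST SEV in between. These figures assume equal SDs at baseline and 6 months and, for SDSS-DAYS, a median cut that the protocol has not yet fixed.

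Three stronger conclusions are not supported:

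- A gap of one standard error for all four scores. Stratification on baseline SDSS-DAYS limits the imbalance in that score, and in SEV and WORST SEV so far as they correlate with it.
- Bias under one of the codings. Both target the same expected treatment difference; what changes is the realised estimate and its precision.
- Treating the power and disagreement percentages as properties of this trial. They rest on an effect borrowed from another outcome and on an assumed correlation.

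The change is worth making because it resolves the ambiguity and costs almost nothing.

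**What to change.** Use one definition of the SDSS and DrInC outcomes in the Outcomes {12} section and in Table 1 rows 2d and 2e, and state the 6-month time point in row 2e. For SDSS DAYS, SEV and WORST SEV and for DrInC total, replace the unadjusted t test as the main analysis with a linear model of the 6-month score on treatment, with the baseline value of the same score as covariate. Report the adjusted mean difference with its 95% confidence interval.

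The cost is a few lines of wording, one covariate per model and the amendment that the protocol requires for changes to the statistical analysis. An outcome defined as change from baseline already requires the baseline scores, and a linear model adjusting for baseline variables is already planned as a sensitivity analysis. No participants, visits or instruments are added.
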